#### 4.7 Cancellation Guidelines

Rev. 9/95

If a patient does not begin assigned treatment, the patient may be canceled. Reasons for cancellation should be submitted in writing to the following offices as soon as possible: For ECOG patients, to the ECOG Coordinating Center (ATTN: DATA); for CALGB patients, to the CALGB Central Office. Data will be collected on all canceled patients (see Section 11.0). **Note:** A patient may only be canceled if no protocol therapy is administered. Once a patient has been given protocol treatment, all forms should be submitted.

Rev. 3/95

For SWOG patients, the SWOG Statistical Center will not consider a patient canceled.

Rev. 8/99

For NSABP patients, the NSABP Biostatistical Center will not consider a patient canceled.

For ACOSOG patients, the ACOSOG Statistical Center will not consider a patient canceled.

## 5.0 TREATMENT PLAN

### 5.1 Surgical Guidelines

#### 5.11 Resection

Please refer to Appendix V: *Technique of Colon Resection*. The colonic tumor must be resected in its entirety. The tumor must not extend below the peritoneal reflection in the area of the rectum. The distal and proximal bowel end must be greater than 5 cm from the tumor. The draining lymph nodes must be removed "en bloc" with the colon specimen. The colon specimen should be sent **immediately** to Pathology upon its removal (see Section 10.0).

- Primary anastomosis or colostomy will be at the discretion of the operating surgeon.
- The procedure must be done as a laparotomy. Resection via a laparoscope will not be acceptable.

#### 5.12 Intraoperative Findings which Prevent Implementation of Protocol Treatment

Patients with isolated, distant, or noncontiguous intra-abdominal metastases at the time of operation (Dukes' D), **even if resected**, are ineligible to receive the designated protocol treatment; they will be followed for survival information. Such extent of intra-abdominal disease must be confirmed histologically. Any suspicious extra-colonic lesion seen at operation should be biopsied. Patients with tumors which require opening of the pelvic peritoneum in order to define the extent of tumor will be considered to have rectal tumors, and are not eligible.

#### 5.13 Pathologic Findings which Prevent Further Chemotherapy

Upon receipt of the final surgical pathology report from the contributing institution's pathology department, Dukes' A, B1, and D patients will have perioperative 5-FU **discontinued**, if so assigned, and will receive NO further adjuvant treatment. These patients will be treated at the discretion of their physician and survival data will continue to be collected on these patients until the time of death. Dukes' B2 patients will have perioperative 5-FU **continued** to completion, if so assigned, but will receive NO further adjuvant treatment. These patients will be followed on observation until relapse or death.

### 5.2 Chemotherapy Guidelines

#### 5.21 Perioperative 5-FU

Patients randomized to the perioperative 5-FU arm must begin treatment within 24 hours of the completion of the curative resection. They will receive 600 mg/m^2/day of 5-FU as a continuous IV infusion over 24 hours for 7 days. Doses of 5-FU should be based on actual weight. See Section 5.41.

Upon receipt of the final surgical pathology report from the contributing institution's pathology department, Dukes' A, B1, and D patient should have perioperative 5-FU chemotherapy **discontinued**. Dukes' B2, B3, and C patients should have perioperative 5-FU **continued** to completion.

Rev. 9/97

## 5.22 Adjuvant 5-FU and Leucovorin

A cycle of therapy will consist of 5 consecutive days of chemotherapy. The full course of adjuvant therapy will consist of 6 cycles.

| Agent | Dose
(per day) | Route | Schedule | Instructions                  |
|--------------|---------------------------|--------------|-----------------|--------------------------------------|
| Leucovorin   | 20 mg/m       | IV push      | days 1-5        |                                      |
| 5-FU         | 425 mg/m      | IV push      | days 1-5        | Give immediately
after Leucovorin |

Dose should be based on actual weight (estimated dry weight if patient has edema).

5.221 Cycles will be repeated at the end of 4 weeks (day 29), 8 weeks (day 57) and then every 4 weeks for a total of 6 cycles.†

| Day
On Study | 1 | 29 | 57 | 85 | 113 | 141 | STOP |
|-------------------------|----------|-----------|-----------|-----------|------------|------------|-------------|
| Treatment
(Days 1-5) | *        | *         | *         | *         | *          | *          |             |

† Initiation of subsequent treatment cycles may be delayed up to 4 days if necessary for logistical reasons.

## 5.3 Adverse Reaction Reporting Requirements

Rev. 3/10

**The descriptions and grading scales found in the revised NCI Common Terminology Criteria for Adverse Events (CTCAE) version 4.0 will be utilized for AE reporting. All appropriate treatment areas should have access to a copy of the CTCAE version 4.0. A copy of the CTCAE version 4.0 can be downloaded from the CTEP web site (<http://ctep.cancer.gov>).**

5.31 This protocol does not contain IND agents; toxicities occurring on this treatment should be considered commercial.

Rev. 9/97

5.32 The following adverse reactions must be reported to ECOG and NCI in the manner described in the table below. In addition your local IRB should be notified.

**NOTE:** CALGB participants should follow ECOG guidelines regarding ADR reporting procedures.

Rev. 3/95

**NOTE:** NSABP participants should follow ECOG guidelines regarding ADR reporting procedures. In addition, a copy of the ADR Form should be forwarded to the NSABP Biostatistical Center.

**NSABP Biostatistical Center Mailing Address:**  
 NSABP Biostatistical Center  
 [name]  
 [name]  
 [name]

For All Drug Arms:

Rev. 8/99

|                                                | Grades 4- 5,
unexpected | Death due to
Rx or within
30 days of Rx |
|------------------------------------------------|------------------------------------------------|--------------------------------------------------------------------|
| ECOG ADR Form to NCI within 10 days            | X                                              | X                                                                  |
| ECOG ADR Form to ECOG DM Office within 10 days | X                                              | X                                                                  |
| Notify local IRB within 10 days                | X                                              | X                                                                  |

-  Any unexpected toxicity not reported in the literature or the package insert must be reported, as well as any increased incidence of a known ADR reported in the package insert or literature.
-  Any death from any cause while a patient is receiving treatment on this protocol or up to 30 days after the last dose of protocol treatment, or any death which occurs more than 30 days after protocol treatment has ended, but is clearly felt to be treatment related, must be reported.

Rev. 9/97  
 Rev. 6/94, 9/95

**NCI [contact]  
**NCI [contact]  

**ECOG Mailing Address:**  
 ECOG Coordinating Center  
 ATTN: ADR  
 Frontier Science  
 [name]  
 [name]

Rev. 3/95, 8/99

Rev. 6/94

ECOG requires ADRs to be reported on the Adverse Reaction (ADR) Form For Investigational Drugs (#391RF). The form must be signed by the treating investigator.

**5.33 Non-Treatment Related Toxicities**

Rev. 9/95, 9/97

Toxicities which fall within the definitions listed above must be reported as an ADR/second primary regardless if they are felt to be treatment related or not. Toxicities unrelated to treatment that do NOT fall within the definitions above, must simply be clearly documented on the ECOG flow sheets which are submitted to the ECOG Coordinating Center (ATTN: DATA) according to the Records to be Kept Section (11.0).

**5.34 All Southwest Oncology Group (SWOG) investigators are responsible for reporting of adverse drug reactions according to the NCI and Southwest Oncology Group Guidelines.**

**SWOG investigators must:**

- Call the SWOG Operations Office at [contact] within 24 hours of any suspected adverse event deemed either drug-related, or possibly drug-related.

Instructions will be given as to the necessary steps to take depending on whether the reaction was previously reported, the grade (severity) of the reaction, study phase, and whether the reaction was caused by investigational and/or commercial agent(s). The SWOG Operations Office will immediately notify ECOG.

**The following ADRs attributed to commercial agent(s) should be reported to the Investigational Drug Branch, Cancer Therapy Evaluation Program, within 10 working days:**

- Any ADR that is both serious (life threatening, fatal) and unexpected.
- Any increased incidence of a known ADR that has been reported in the package insert or the literature.
- Any death on study if clearly related to the commercial agent(s).

The adverse reaction must be documented on the ECOG ADR Form (#391RF) and a copy mailed to:

Investigational Drug Branch  
 [name]  
 [name]

In addition, within 10 days the investigator must send:

- the original of the above ADR report
- all data records for the period covering prestudy through the adverse event
- documentation of IRB notification, to the following address:

ADR Program  
 SWOG Operations Office  
 [name]  
 [name]

At the Operations Office, a multilayered review will be performed and any pertinent findings will be forwarded to ECOG, the NCI Study Coordinator, and Statistical Center, along with any supporting documentation. The original should be sent whenever forwarding an ADR Form to ECOG.

5.35 The following adverse reactions must be reported to ACOSOG, the NCI, and your local IRB in the manner described below:

For all Drug Arms:

|                                                              | Grade 4-5
unexpected | Death due to
Rx or within
30 days of Rx |
|--------------------------------------------------------------|---------------------------------|--------------------------------------------------------|
| ADR Form 391 RF to NCI within 10 days                        | X                               | X                                                      |
| ADR Form 391 RF to ACOSOG Coordinating Center within 10 days | X                               | X                                                      |
| Notify local IRB within 10 days                              | X                               | X                                                      |

- 1 Any unexpected toxicity not reported in the literature or the package insert must be reported.
- 2 Any death from any cause while a patient is receiving treatment on this protocol or up to 30 days after the last dose of protocol treatment, or any death which occurs more than 30 days after protocol treatment has ended but which is felt to be treatment related, must be reported.

All ADRs should be reported on the Adverse Reaction (ADR) Form for Investigational Drugs (#391RF). The form must be signed by the treating investigator and faxed to the ACOSOG Coordinating Center at **[contact]** or **[contact]**. A copy should be sent to NCI.

**NCI [contact]

**NCI [contact]

5.36 Non-Treatment Related Toxicities

Toxicities which fall within the definitions listed above must be reported as an ADR/Second primary regardless if they are felt to be treatment related or not. Toxicities unrelated to treatment that do NOT fall within the definitions above must simply be clearly documented on the ECOG Toxicity Form and faxed to the ACOSOG Coordinating Center.

5.4 Dose Modifications

Rev. 3/10

**NOTE:** Dose modifications are defined using CTC Version 2 terminology (see Appendix II).

5.41 Drug Toxicity and Cessation of Perioperative 5-FU Therapy \*

No dose modification will be implemented; infusions will be discontinued if any of the following reactions are apparent:

Rev. 8/99

- (a) Leukocytopenia ( $< 3000/\text{mm}^3$ )\*
- (b) Thrombocytopenia ( $< 100,000/\text{mm}^3$ )\*
- (c) An intervening significant postoperative complication
- (d) If patient develops angina, thought to be secondary to 5-FU, the infusion should be discontinued.
- (e) Grade II mucositis

Rev. 8/99

\* WBC, PLT will be checked on post-operative day 2 and day 5.

Rev. 9/97

#### 5.42 Dose Modifications During Treatment with 5-FU + Low-Dose Leucovorin

Rev. 3/10

**NOTE:** Dose modifications are defined using CTC Version 2 terminology (see Appendix II).

If multiple toxicities are seen, the dose administered should be based on the most severe toxicity experienced. Dosage reductions apply to the dose of chemotherapy given on the preceding treatment cycle, and should be based on toxicities observed since the previous dose of chemotherapy. (The dose of leucovorin is not modified for chemotherapy toxicity.)

##### 5.421 Toxicity Based on Interval Toxicity

| Toxicity                            | Percent of Dose Resulting In Toxicity |                   |
|--------------------------------------------|----------------------------------------------|-------------------|
|                                            | 5-FU                                  | Leucovorin |
| Hematology Nadirs (/mm^3) |                                              |                   |
| WBC 1000-2500                              | 80%                                          | 100%              |
| WBC < 1000                                 | 70%                                          | 100%              |
| PLT 25,000-75,000                          | 80%                                          | 100%              |
| PLT < 25,000                               | 70%                                          | 100%              |
| Diarrhea                            |                                              |                   |
| CTC Grade 1                                | 100%                                         | 100%              |
| CTC Grade 2                                | 80%                                          | 100%              |
| CTC Grade 3-4                              | 70%                                          | 100%              |
| Stomatitis                          |                                              |                   |
| CTC Grade 1                                | 100%                                         | 100%              |
| CTC Grade 2                                | 80%                                          | 100%              |
| CTC Grade 3-4                              | 70%                                          | 100%              |

IF WBC < 3,500/mm^3 and or platelets < 100,000/mm^3 at the start of a treatment cycle, hold therapy and repeat counts weekly x 2. If the blood counts are still below these levels, adjuvant therapy should be discontinued.

*The dose of 5-FU may be re-escalated only in patients experiencing Grade 1 diarrhea or mucositis and for hematologic toxicity, provided they have not had toxicity based on the most prior treatment. The drug should be re-escalated to the next highest dose level.*

Rev. 9/97

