## 5.52 Supportive Care Options During Therapy with 5-FU + Leucovorin

Rev. 9/97

Diarrhea has been a common toxicity with 5-FU + Leucovorin therapy, frequently requiring parenteral hydration and significant dose delays and modifications. Preliminary reports suggest that somatostatin analogue (Sandostatin) may more rapidly and completely control diarrhea, which may lead to better protocol compliance and safety (25).

Rev. 9/97, 8/99

Method: In patients with  $\geq$  Grade 1 diarrhea, chemotherapy should be modified as appropriate by protocol. In addition, patients who have  $\geq$  Grade 2 diarrhea should be considered for Sandostatin therapy, 50-100 ug SQ every 8 hours for up to 3 days. When utilized, Sandostatin therapy and response should be recorded on flow sheets.

ECOG investigators may wish to consider entering patients with at least Grade 2 chemotherapy-related diarrhea on E1295, *Randomized Trial of High-Dose Versus Conventional Dose Octreotide Acetate Versus Loperamide In The Treatment of Chemotherapy-Related Diarrhea In Patients With Colorectal Cancer*.

Appropriate dose modifications should continue to be implemented in subsequent treatments, based on the highest grade of diarrhea experienced.

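### Protocol Section 5.421's re-escalation sentence does not fit its own table, and Sections 5.42 and 5.52 can give different 5-FU doses after repeated diarrhea

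*Protocol*

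**What the plan says.** Four parts of the Protocol govern the adjuvant 5-FU dose.

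- **Section 5.22** sets the starting dose at 425 mg/m2 per day on days 1-5.
- **Section 5.42** gives the base and the time window. "Dosage reductions apply to the dose of chemotherapy given on the preceding treatment cycle", and they "should be based on toxicities observed since the previous dose of chemotherapy".
- **Section 5.421** gives the percentages under the column heading "Percent of Dose Resulting In Toxicity". For both diarrhea and stomatitis, 5-FU is 100% at Grade 1, 80% at Grade 2 and 70% at Grade 3-4. Below the table, re-escalation is restricted: the drug "may be re-escalated only in patients experiencing Grade 1 diarrhea or mucositis and for hematologic toxicity". A further condition is attached to this permission, namely "provided they have not had toxicity based on the most prior treatment". The step is then given: "The drug should be re-escalated to the next highest dose level".
- **Section 5.52**, on supportive care for diarrhea, says that from Grade 1 upward "chemotherapy should be modified as appropriate by protocol". It closes by saying that modifications carry on into later treatments, "based on the highest grade of diarrhea experienced".

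**The concern.** There are two separate problems.

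The first lies within Section 5.421. For gastrointestinal toxicity, the only grade named as eligible for re-escalation is one that the table never reduces for. The added condition then requires that the patient had no toxicity at the latest treatment. A site cannot tell from this whether a reduction made for diarrhea or stomatitis may ever be reversed. Where re-escalation is allowed, the site cannot tell how large the step is.

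The second lies between Sections 5.42/5.421 and Section 5.52, and concerns diarrhea only. One rule looks back over a single interval and the other at the worst grade so far. When the grade falls from one cycle to the next, the two can give different doses.

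Dosing safety is at stake, as is the uniformity of the adjuvant treatment that both arms share. Section 5.52 itself describes diarrhea as common with this regimen, so the situation will arise.

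**Working it through.** The Protocol states no figure to reproduce here, so the check applies each written rule to the same patient.

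**Inputs.** Starting dose 425 mg/m2/day (Section 5.22). Factors from the Section 5.421 table: Grade 0-1 = 1.0, Grade 2 = 0.8, Grade 3-4 = 0.7. Stomatitis in the table and mucositis in the re-escalation sentence are taken as the same toxicity.

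**Step 1: the re-escalation sentence against its table.**

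- Patient with Grade 1 toxicity only: 425 x 1.0 = 425. No reduction exists, so there is nothing to re-escalate.
- Patient reduced earlier for Grade 2 or worse who now has Grade 1: the sentence names this patient, but the condition excludes them, because Grade 1 is itself toxicity at the latest treatment.
- Patient reduced for Grade 2 or worse who now has no toxicity: the condition is met, but the patient is not experiencing Grade 1, so the word *only* appears to shut them out. That would make such reductions permanent, which the text does not say.

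**Step 2: the size of the step.** Section 5.42 lists percentages of the preceding dose and no dose levels. A patient cut to 70% for a hematologic nadir receives 425 x 0.7 = 297.5. The next level up could be the table's 80% step, 425 x 0.8 = 340, or the dose given before the cut, 425.

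**Step 3: interval toxicity against worst grade.** Formulas for the cycle 3 dose:

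- Sections 5.42/5.421: cycle 2 dose x factor for the toxicity after cycle 2.
- Section 5.52, preceding-dose base: cycle 2 dose x factor for the worst grade so far.
- Section 5.52, starting-dose base: 425 x factor for the worst grade so far.

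The cycle 2 dose is 425 x 0.7 = 297.5 after Grade 3, 425 x 0.8 = 340 after Grade 2, and 425 after Grade 1.

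| Diarrhea after cycle 1, then cycle 2 | 5.42/5.421 | 5.52, preceding-dose base | 5.52, starting-dose base |
|---|---|---|---|
| Grade 3, then Grade 2 | 297.5 x 0.8 = 238 | 297.5 x 0.7 = 208.25 | 425 x 0.7 = 297.5 |
| Grade 2, then none or Grade 1 | 340 x 1.0 = 340 | 340 x 0.8 = 272 | 425 x 0.8 = 340 |
| Grade 1, then none or Grade 1 | 425 | 425 | 425 |

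In the first row Section 5.52 differs from Sections 5.42/5.421 under either base: by 297.5 - 238 = 59.5 mg/m2/day upward, or 238 - 208.25 = 29.75 downward. As shares of the starting dose these are 59.5/425 = 14% and 29.75/425 = 7%. In the second row the rules agree if Section 5.52 means holding the reduced dose. In the third row they always agree.

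**The case against.** The strongest reply is that the sections mostly agree. Section 5.42 applies reductions to the preceding cycle's dose, so a reduction persists by default, and Section 5.52 also asks for persistence. Its reference to the highest grade closes a passage on octreotide, and may mean only that diarrhea is graded at its worst even if supportive care then controls it. On that reading both give 238 in the first row. The lower figures, 208.25 and 272, re-apply an old toxicity's percentage to a dose already cut, which sits badly with the table's column heading. The starting-dose base is not written into Section 5.52 either. Finally, the re-escalation sentence is permissive and its hematologic part can operate; if the gastrointestinal part has nothing to act on, the result is no re-escalation rather than two doses.

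Much of this stands. For Grade 2 followed by no toxicity, holding at 340 satisfies every section, and the re-escalation sentence alone does not produce conflicting doses. But restricting the highest grade to the last interval fits poorly with an instruction about continuing modifications in subsequent treatments. That Section 5.52 names no base is part of the problem, since neither candidate base gives 238. The hematologic part still depends on undefined dose levels.

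Two stronger readings are tempting. A reader might infer that Section 5.52 changes the dose at Grade 1. It does not: "chemotherapy should be modified as appropriate by protocol" defers to the table, which gives 100%. A reader might also infer that up to 20 points of dose after Grade 2 diarrhea, or 30 points after Grade 3-4, turn on whether the dose is held or raised. No section clearly permits raising it after Grade 2-4 diarrhea: the sentence is limited to Grade 1, and a return to 425 with current Grade 1 is barred by its own condition.

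**Conclusion.** The point holds as a wording defect of limited reach. The re-escalation sentence in Section 5.421 is inconsistent with the table above it for gastrointestinal toxicity, and its step is undefined. For diarrhea, Sections 5.42/5.421 and Section 5.52 can give different doses when a lower-grade event follows a higher-grade one: 238 against 297.5 or 208.25 mg/m2/day in cycle 3 after Grade 3 and then Grade 2.

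The dose difference assumes that Section 5.52 refers to the worst grade over all cycles so far, which is its more natural reading but not the only one. The Protocol does not say how often this sequence of grades is expected, so the number of patients affected cannot be given.

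The defect concerns only adjuvant 5-FU/leucovorin in Dukes' B3 and C patients. The perioperative infusion is outside it, since Section 5.41 allows no dose modification there. The same rules apply in both arms, so the text gives no ground for inferring bias between them, and the sample size, power and alpha in Section 9.0 are untouched.

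**What to change.** Reconcile Sections 5.42, 5.421 and 5.52 so that one rule states:

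1. which toxicity period governs the next dose;
2. to which base dose the percentage applies;
3. when, if ever, a reduction for gastrointestinal toxicity may be reversed;
4. what the dose levels are, if re-escalation by level is kept.

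A worked example for Grade 3 followed by Grade 2 diarrhea would show sites that the rule gives a single answer. The sponsor decides which clinical rule is right; this review takes no view. The cost is a clarifying change of wording in Sections 5.4 and 5.5, with no statistical cost.
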